**Methods:**

An open cohort stepped wedge cluster randomized trial in inpatients psychiatric wards of GGz Centraal, the Netherlands. The wards are divided into three clusters based on geographical region. These clusters are randomly allocated to one of the three pre-defined steps to integrate MULTI + . MULTI + can be tailored to fit individual psychiatric wards and includes 10 core components aimed at improving lifestyle factors. The primary outcome is to investigate the difference in the mean QRISK3 score of patients receiving MULTI + compared to patients receiving TAU. Secondary outcomes include somatic and mental health outcomes, lifestyle factors, and implementation factors. Findings will be analysed using mixed model analyses.

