## Methods

### Study design and setting

This study is an open cohort stepped wedge cluster randomized trial conducted at all inpatient wards of the specialist mental healthcare organisation GGz Centraal (the Netherlands) [34]. The organisation will implement MULTI + semi-annually in three geographical regions (clusters). Wards are almost equally distributed per cluster, covering a total of ~ 830 places of residence in which ~ 2000 patients are treated annually (Table 1). This gradual implementation intends that all clusters are exposed to MULTI + at the end of this trial. Each step includes a one-month transitional phase to prepare the cluster for the implementation of MULTI + . This trial takes 18 months to complete.

**Table 1 Tab1:** *Places of residence divided in three clusters*

**Cluster**	**Wards (n)**	**Places of residence (n)**
1	15	~ 300
2	14	~ 300
3	15	~ 230

In line with the regional implementation, cluster-level randomisation is used. Individual-level randomisation is not possible because patients cohabit in groups within wards. Moreover, cluster-level randomisation minimizes the risk for contamination between HCPs working in multiple wards or different geographical clusters. Due to high patient turnover the patient population may differ at each measurement and individual follow-up for long-term evaluation is not feasible after discharge.

Measurements are obtained at the same time in all clusters at baseline (T0), after six months (T1), after twelve months (T2) and after eighteen months (T3). Measurements take approximately three months to complete (Fig. 1).

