### Statistical analyses

Within each cluster-intervention period (cluster I and TAU, cluster I and MULTI + , cluster II and TAU, cluster II and MULTI + etc.) we will analyse the QRISK3 of patients treated in that period. We select the last known measurements for each patient (longest exposure). For each of these measurements, the duration of exposure of patients in this cluster is calculated (date of last measurement minus day of entering this period). A proportion of patients will experience the switch in intervention during their stay. In such individuals, we will analyse both measurements reflecting the different conditions. The correlation of between subject measurements will be taken into account by adding a random effect for subjects. All QRISK3 data points will be analysed with mixed model analyses. We will analyse the logit transformed QRISK3 probabilities for similar reasons as in logistic regression, namely to avoid problems of estimating probabilities below 0 or above one and because it is more likely that the effect of treatment and other covariates on the outcome will be constant on the relative odds ratio scale.

The linear mixed model will contain: treatment (binary, 1/0 coding), cluster (categorical, two levels, dummy variables), time period (categorical, four levels, dummy variables), random effect for subject, the duration of exposure (continuous, restricted cubic splines with three knots); and the following potential confounding variables: age (continuous), key diagnostic subgroups (categorical) and illness severity (continuous).

Multiple imputation will be used to account for missing values. The same variables will be used in the imputation model as in the analysis model, extended with characteristics related to these variables. Multiple imputation based on chained equations will be used to generate 10 imputation sets (or more if the number of missing values is larger than expected). Results from imputed datasets will be pooled using Rubin’s rules.

Although MULTI + will be integrated into routine clinical care regardless of specific inpatient facility setting, we pragmatically set a minimum of 10 days exposure, assuming that we cannot expect an effect within a few days of hospitalization.

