Explorative subgroup analyses will be performed to gain insight in possible treatment differences between the subgroups gender (categorical) age (continuous) and subjects with repeated-measures. Subgroup analyses will be performed consecutively by adding the main effect of these variables and their interaction to the main model specified above.

All analyses will be conducted with IBM SPSS statistics 25 and R version 4.0.4 or higher, with a 95% confidence interval (*p* < 0.05) and will be corrected for multiple outcomes/comparisons (Bonferroni correction) if necessary.

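### Membership of the repeated-measures subgroup is settled after allocation, so its treatment interaction mixes effect modification with selection and in-stay drift

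*Protocol article*

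**What the plan says.** All of the following is in the Protocol article, Statistical analyses, unless stated otherwise.

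- **Subgroups.** The analyses are labelled exploratory ("Explorative subgroup analyses will be performed to gain insight") and look for "possible treatment differences between the subgroups gender (categorical) age (continuous) and subjects with repeated-measures".
- **Method.** All three variables are handled alike: "Subgroup analyses will be performed consecutively by adding the main effect of these variables and their interaction to the main model specified above".
- **Which values are analysed.** Within each combination of region and condition the rule is "We select the last known measurements for each patient (longest exposure". On patients present at the changeover: "A proportion of patients will experience the switch in intervention during their stay", and "In such individuals, we will analyse both measurements reflecting the different conditions".
- **Setting.** Regions, not patients, are allocated to the steps (Abstract, Methods). Study design and setting adds: "Due to high patient turnover the patient population may differ at each measurement and individual follow-up for long-term evaluation is not feasible after discharge". Under Procedural considerations, data collection stops at discharge or death, and data already collected are kept.

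The article does not define the repeated-measures subgroup separately, and it does not say how its interaction may be read.

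**The concern.** Gender and age are known when a patient enters the study. Having two analysed values is not. It depends on still being an inpatient, and being measured, after the region's switch, and the date of that switch is itself what was randomised. For a usual-care value, the patient's stratum is decided by what happens later. For a MULTI+ value, it is decided by what happened before.

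The two strata then hold different kinds of comparison, and a treatment-by-stratum interaction subtracts one from the other. At stake is a secondary message: the trial could report that MULTI+ works better or worse in patients followed across the switch when the difference reflects who stays, or how risk moves during a stay. The primary estimate does not use this term.

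**Working it through.** The documents give no figure for this subgroup, so there is nothing to reproduce. The check has three parts.

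**1. What the interaction estimates.** Let R = 1 for patients with a value under both conditions and x = 1 for MULTI+. After adjustment for cluster and period:

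- In R = 1, the treatment contrast δ₁ is a within-person change, always usual care first and MULTI+ later in the same stay. The patient's own level cancels.
- In R = 0, the contrast δ₀ compares patients with only a MULTI+ value (mostly admitted after the switch) with patients with only a usual-care value (mostly gone before it).
- The interaction is δ₁ − δ₀.

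With no treatment effect and no modification, δ₁ still contains drift in stayers, and δ₀ still contains any difference in level and in time since admission between entrants and leavers.

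**2. What the model terms remove.** Period terms are common to both strata, so they do not absorb a time course specific to stayers. Exposure is counted from entry into the current cluster-intervention period. It restarts at the switch, so a long-stay patient and a new admission can have the same MULTI+ exposure. Time since admission is not in the model. Age, diagnosis and illness severity may remove part of the selection.

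**3. How large it could be.** Two simulations were run with true effect 0 and true interaction 0. Length of stay, drift and variances are assumptions, because the document gives none of them.

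*Simulation A: risk level related to total length of stay.* From the document: 300/300/230 places, measurements at 0, 6, 12 and 18 months, last value per condition, at least 10 days of exposure. Assumed: switches at 1.5, 7.5 and 13.5 months; half the beds with mean stay 3 months and half 30 months; between-person SD 1 and residual SD 0.3 on the logit scale; risk rising by b per log-month of stay. Turnover check: 415 × 12/3 + 415 × 12/30 = 1,660 + 166 = 1,826 a year, against about 2,000 stated. The fitted model used linear and log exposure in place of the plan's spline and had no age, diagnosis or severity terms. Each scenario had 80 runs, with about 380 patients with two values and about 1,580 with one.

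| b | Mean interaction (logit) | exp(interaction) | Rejected at 5% |
|---|---|---|---|
| 0 | +0.003 | 1.00 | 3/80 = 3.8% |
| 0.4 | −0.046 | 0.96 | 10/80 = 12.5% |
| 0.8 | −0.095 | 0.91 | 20/80 = 25% |

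The Monte Carlo standard error of the last two rates is √(0.125 × 0.875/80) = 3.7 points and √(0.25 × 0.75/80) = 4.8 points.

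*Simulation B: risk drifting during the stay.* Assumed: 830 places, 60% with mean stay 3 years and 40% with mean stay 66 days; drift of 0.10 logit per six months in the first year; 40 runs. Turnover check: 498/3 + 332 × 365/66 ≈ 166 + 1,836 = 2,002 a year.

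- Mean time since admission, capped at one year, went from 0.82 to 0.97 years (+0.15) between the usual-care and MULTI+ values in stayers, and from 0.35 to 0.26 years (−0.09) in the other stratum.
- Expected false interaction without exposure adjustment: [0.15 − (−0.09)] × 0.20 per year = 0.048. With all measurements kept and no exposure term, the simulation gave +0.052.
- With the plan's last-value rule and an exposure spline it was +0.050 if usual-care exposure is counted from admission, and −0.002 if counted from trial start.
- Without drift it lay between −0.02 and +0.01.

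The two mechanisms give opposite signs, and each can give almost nothing.

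**The case against.** **The definition is inferred.** The article names the subgroup without defining it, and a full protocol or analysis plan may do so. This stands as a caution. But the one-value-per-condition rule leaves no other evident source of repeats, and the choice to test it beside gender and age is stated.

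**The strata are not purely stayers, leavers and entrants.** Some single-value patients were present on both sides but measured on only one, through refusal or too short an exposure. This stands, hence the word mostly.

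**Stronger readings are not supported.** A reader might infer the following:

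- *The interaction is itself a comparison of early leavers with late entrants, and can show nothing about treatment.* Only the single-value stratum has that form. The other is a genuine within-person comparison, and the bias vanishes if stay and in-stay drift are unrelated to risk given the covariates.
- *The plan has a bias of 0.05 and a false-positive rate of 15–17%.* That rate assumes a bias of one standard error, the top of the 0.00 to +0.05 that Simulation B gave with the plan's selection and spline. At the other end it is about 5%. Neither simulation is described as adjusting for age, diagnosis and severity.
- *MULTI+ alters membership by altering length of stay.* Reaching the switch is settled under usual care. MULTI+ could act only between the switch and the next qualifying measurement, and nothing in the document suggests that it changes length of stay.

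**The analysis is exploratory.** No decision is tied to it. This stands and sets the severity, but it does not make the interaction interpretable.

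**Conclusion.** The point holds as a minor one. The repeated-measures variable is fixed by staying in care and being measured across the switch, yet it is tested as though it were a baseline trait. Its interaction cannot tell effect modification from selection or in-stay drift.

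Under the assumed lengths of stay and drift, the mean spurious interaction in models with the last-value rule and an exposure adjustment ran from −0.095 to +0.050 logit, a ratio of odds of about 0.91 to 1.05, including values near zero. These figures show that the problem can arise and that its direction cannot be predicted. They do not estimate the bias in this trial. The primary treatment estimate and the gender and age interactions are not touched by this point.

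**What to change.** Remove the repeated-measures variable from the treatment-by-subgroup interactions, leaving gender and age. In its place, refit the main model in patients with an analysed value under both conditions, keeping the cluster and period terms. Label the result a sensitivity analysis of within-person change in patients who stayed across the switch, and state that it is not evidence of a differential treatment effect. A plain before-after change would be a poorer substitute, because it loses the period adjustment.

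If a stay-related subgroup is wanted, define it by a characteristic known at entry. Ward type is a candidate, but Table 1 gives only numbers of wards and places, so a long-stay or short-stay classification would have to be drawn up first.

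The cost is one exploratory interaction and a sentence or two of text, with no new data. Precision may be poor. If the switches follow T0, T1 and T2 in turn, every region is under MULTI+ at T3. Patients who stay to the end then have their last MULTI+ value at T3, where no usual-care value exists, so separating treatment from period rests on those whose last MULTI+ value is at T1 or T2. Report how many there are, or use all measurements of these patients in this sensitivity analysis.

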### Sample size

Our sample size considerations are based on demonstrating a difference in body weight between conditions. The reason is that we did not have any relevant data on changes in QRISK3 for this population, whereas body weight has been used in our previous research [32]. Furthermore, body weight is a key component of the QRISK3 and, given the nature of MULTI + , it is likely that other components of the QRISK3 will change in the same direction. Therefore, using body weight can be seen as a more robust and more conservative approach than using uncertain assumptions about changes in QRISK3.

Our research showed that 53.8% of the patients who participated in MULTI lost ≥ 5% of their initial bodyweight, as opposed to 16.3% of the patients who followed TAU. Given the broader implementation of MULTI + , with patients who spend less time in healthcare than those in the earlier study, we expect to find effects in a relative smaller number of patients in this study. Based on a small-scale follow-up, we will assume 32% of patients will lose ≥ 5% of their initial bodyweight instead of 53.8%. Because metabolic risk factors are a routinely measured outcome, we expect a conservative dropout rate of 10%. Because there is insufficient knowledge about the correlations between clusters, we will assume a correlation of 0.1. Based on these data, a power of 80%, a significance level of 5% (*p* < 0.05), three clusters, the minimal sample size should consist of 846 patients. Given the high patient turnover (n≈2000), this seems feasible.

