## Discussion

This study protocol has been designed to evaluate the effectiveness and implementation of MULTI + in a specialist mental healthcare organisation with ~ 830 places of residence. To our knowledge, this will be the first large-scale study evaluating the long-term effects of a multidisciplinary, multicomponent approach aimed at improving lifestyle factors in routine inpatient clinical care. This study builds on previous research, which showed improvements on both physical and mental health outcomes in patients, and the need for more organisational support to continue and expand its implementation [32].

A reduction of ≥ 5% loss of body weight is associated with a relevant reduction in cardiovascular risk [60], which we therefore originally considered as the primary outcome of this study [61]. However, this was reconsidered after observing the high-patient turnover hindering individual follow-up and several other substantive considerations. Predominantly, this outcome measure does not account for other known risk factors for developing CVD, such as familial history, age, smoking behaviour, total cholesterol level, presence of mental illness and the use of atypical antipsychotics. By not taking these risk factors into account, the risk of CVD is often underestimated in people with MI and outcomes can be misinterpreted (e.g., lack of weight loss while reducing smoking behaviour) [62]. QRISK3 is a risk calculator that estimates individual risk of developing CVD in people between 25–84 years old, using multiple predictor variables that are especially relevant for people with MI. Therefore, the primary aim of this study is to investigate the difference in the mean QRISK3 score of patients receiving MULTI + compared to patients receiving TAU. To our knowledge there are no risk calculators suitable for ages under 25. Inpatients < 25 will therefore be excluded from this analysis, but will be included for secondary outcomes.

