The study protocol should be viewed considering several limitations. A first limitation is the risk of missing data. For example, not all patients may be able to complete all questionnaires due to illness severity and cognitive deficits. Therefore, semi-structured interviews will be used to allow for more flexibility and clarification. Another reason for missing data could be patients refusing the administration of the routine screening. Moreover, some routine measurements are only assessed on clinical indication, and will not be present for each patient.

Another limitation is that implementation monitoring could be a challenge because of the large-scale, real-world conditions of the study. Furthermore, external events and organisation-wide changes may impact the effectiveness and implementation of MULTI + due to the non-controlled environment and may be difficult to account for.

Strengths of this study are that MULTI + allows for pragmatic implementation in real-world settings through co-design and tailoring of the 10 core components. We expect that this approach will increase long-term sustainability and can serve as a potential blueprint. Additionally, studying implementation factors will expand our knowledge on how to overcome the implementation gap and successfully implement a lifestyle intervention. Furthermore, we research a broad spectrum of both physical and mental health outcomes in inpatients with MI. This dual research focus on both implementation factors and health outcomes will expand our knowledge on the possible influences these factors have on one another. Ultimately, we aim to improve routine clinical care for inpatients with mental illness.

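### The 846 patients and 80% power apply to 5% weight loss, the former primary outcome; the power for QRISK3 is unknown, and calling body weight the conservative basis is unsupported

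*Protocol article*

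**What the plan says.** Under Primary outcome, the protocol article names the difference in mean QRISK3 between MULTI+ and usual care. Under Statistical analyses, the logit of QRISK3 enters a linear mixed model with treatment, cluster, period, a subject effect, duration of exposure and covariates.

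The Sample size section rests on something else: "Our sample size considerations are based on demonstrating a difference in body weight between conditions". The control rate comes from the group's earlier study, which found that 53.8% lost at least 5% of body weight under the predecessor programme, "as opposed to 16.3% of the patients who followed TAU". For this trial, "we will assume 32% of patients will lose ≥ 5% of their initial bodyweight instead of 53.8" per cent. With 80% power, 5% significance, a correlation of 0.1, 10% dropout and "three clusters, the minimal sample size should consist of 846 patients".

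The section explains that no relevant QRISK3 data existed for this population. It expects other QRISK3 components to move in the same direction as weight, and concludes that "using body weight can be seen as a more robust and more conservative approach than using uncertain assumptions about changes in QRISK3".

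The Discussion says that weight loss of at least 5% was first considered as the primary outcome, and that "this was reconsidered after observing the high-patient turnover hindering individual follow-up", among other reasons. It also says that patients under 25 are left out of the QRISK3 analysis. Statistical analyses sets a minimum exposure of 10 days.

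**The concern.** A power figure belongs to one endpoint, one effect size and one analysis. Here it belongs to a binary within-person change, while the primary analysis compares a continuous risk score between and within patients. A proxy endpoint is conservative only if its standardised effect is no larger than that of the outcome it stands in for. Judging this needs at least an assumed QRISK3 difference and SD, and the article gives neither.

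The article's own Discussion also weakens the argument that weight and the other components move together. Among its reasons for dropping the weight endpoint is that smoking may fall without any weight loss.

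At stake is how a null result is read. A reader who carries the 80% over to QRISK3 would take a null finding as fairly strong evidence of no effect, and the document gives no basis for that.

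**Working it through.** **1. Reproducing 846.** Inputs from Sample size: 0.163 and 0.32, power 80%, significance 5% (two-sided assumed), 10% dropout, three clusters.

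- Mean proportion: (0.163 + 0.32)/2 = 0.2415. Difference: 0.157.
- Per arm, without continuity correction: [1.960 × √(2 × 0.2415 × 0.7585) + 0.842 × √(0.163 × 0.837 + 0.32 × 0.68)]² / 0.157² = 115.5, so 116.
- With continuity correction: (115.5/4) × [1 + √(1 + 4/(115.5 × 0.157))]² = 127.9, so 128. Two arms: 256.
- Dropout: 256 × 1.10 = 281.6, so 282. Times 3: **846**.

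The factor 3 is inferred. It could be the number of clusters, or a design effect of 1 + (21 − 1) × 0.1 = 3. A stepped-wedge design-effect route without continuity correction gives 831, within 3%. By either route, 846 is a two-proportion calculation for weight loss of at least 5%.

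**2. What a QRISK3 calculation would need.** It needs a difference, an SD and a correlation on the logit scale. The article gives no difference and no SD, so no QRISK3 sample size or power can be derived from it.

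**3. Illustration in SD units.** Assumptions: three clusters by four measurement rounds; all clusters on usual care at T0, then one more cluster exposed at each round; equal cells; one observation per patient; 846 × 0.9 = 761.4 evaluable, so m = 761.4/12 = 63.45 per cell.

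With cluster and period as fixed effects, as in the stated model, the sum of squares of the treatment indicator is:
- total: 12 × 0.25 = 3
- between clusters (means 0.75, 0.5, 0.25): 4 × (0.0625 + 0 + 0.0625) = 0.5
- between periods (means 0, 1/3, 2/3, 1): 3 × (0.25 + 0.0278 + 0.0278 + 0.25) = 1.667
- residual: 3 − 0.5 − 1.667 = 0.833

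The variance of the treatment effect is σ²/(0.833 m) = 1.2σ²/m. At m = 63.45, SE = √(1.2/63.45) = 0.1375 SD. The detectable difference at 80% power is (1.960 + 0.842) × 0.1375 = **0.385 residual SD**. For 2000 patients, m = 166.7, SE = 0.0849, and the detectable difference is **0.24 SD**.

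With a random cluster effect (Hussey-Hughes variance) instead, intracluster correlations of 0.01, 0.05 and 0.10 give 0.355, 0.368 and 0.362 total SD at 761 patients, and 0.22 to 0.23 at 2000.

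**4. Power at 761 evaluable patients** (random-effect version, correlations 0.01 to 0.10):

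| True difference (SD of logit QRISK3) | Power |
|---|---|
| 0.1 | about 12% |
| 0.2 | 33–35% |
| 0.3 | 63–66% |
| 0.4 | 86–89% |

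So the adequacy of 846 depends wholly on an effect size that the article does not state.

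**5. Exclusions.** The 10% is described as dropout. The age and exposure exclusions from the primary analysis come on top. If a fraction f is excluded, the detectable difference grows by 1/√(1 − f). The article gives no figure for f.

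**The case against.** The strongest defence is openness. The section begins by naming body weight as its basis and admits the lack of QRISK3 data, and the Discussion explains the change of primary outcome. A careful reader will not mistake the 80% for QRISK3 power. This stands: nothing is hidden, and the arithmetic of 846 is not at fault. It does not rescue the conservatism claim, which is an affirmative statement without a calculation behind it.

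The illustration is also open to challenge. The 846 is a minimum, and the article cites about 2000 patients treated annually. Patients who switch condition contribute two measurements, and adjustment for age lowers the residual SD. All of this could improve precision. In the other direction, unequal cells, the exclusions and adjustment for exposure duration could reduce it. The SD figures therefore show scale only.

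Some stronger readings are tempting but not supported:

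- *The trial is underpowered for QRISK3.* The power is unknown, which is not the same as low.
- *The design cannot follow individuals at all.* The article says that turnover hinders follow-up, and it expects some patients to be measured under both conditions.
- *Weight is never looked at again.* Weight in kg remains among the routine measures. Only the 5% responder version is not listed, and this is a condensed article.
- *The 10% dropout contradicts the statement that* "some routine measurements are only assessed on clinical indication, and will not be present for each patient". That sentence does not say that QRISK3 components are the measurements concerned, and multiple imputation is planned.

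**Conclusion.** The point holds as a mismatch between the stated power and the primary analysis, together with an unsupported claim of conservatism. That 846 is a weight-loss calculation is firm, because the figure reproduces exactly under a two-sided continuity-corrected test, given the inferred factor of 3. The absence of any QRISK3 difference or SD is plain from the text.

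The size of the consequence cannot be fixed from the document. The range of about 0.35 to 0.39 SD at 761 patients, and about 0.24 SD at 2000, rests on equal cells, one observation per patient and the assumed rollout pattern. Whether lifestyle change could move logit QRISK3 that far is not something the article allows one to judge.

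**What to change.** In the Sample size section:

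1. State that the 80% power with 846 patients refers only to the proportion losing at least 5% of body weight, and not to QRISK3.
2. Delete the sentence that presents body weight as the sturdier and more cautious basis.
3. Report the minimum detectable difference on the logit QRISK3 scale for the primary model. Use the SD and completeness of the T0 data pooled over clusters, at the number expected to remain after the age and exposure exclusions.

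T0 is the baseline round in every cluster, and pooling over clusters means that the calculation reveals no treatment effect. The article says that data collection has already started.

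The cost is one calculation, some rewording and a less favourable power statement. The correction requires no extra patients and no change in conduct.
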